# Safety of Postpartum Herbal Medicine in Primary Care Korean Medicine Clinics: Protocol for a Prospective, Multicenter, Registry-Based Observational Study

**DOI:** 10.2196/87543

**Published:** 2026-04-17

**Keywords:** postpartum period, herbal medicine, safety, adverse events, registry

## Abstract

**Background:**

Postpartum conditions significantly affect maternal and infant health. In South Korea, herbal medicine is commonly used for postpartum care in Korean medicine, but safety data remain limited. This study outlines a multicenter Korean medicine clinic registry designed to investigate treatment patterns and adverse events (AEs) associated with postpartum herbal medicine use. This primary care, practice-based research network registry will inform clinical decision-making and pharmacovigilance in postpartum care, supporting the quality and safety of care and guidance for comedication monitoring across community clinics.

**Objective:**

This study aims to establish a multicenter registry to investigate AEs and treatment patterns associated with postpartum herbal medicine use in Korean medicine clinics.

**Methods:**

This prospective observational registry will enroll postpartum patients receiving herbal medicine treatment from 15 Korean medicine clinics between July 2024 and June 2027, with a target sample size of 1000 participants. Patients within 6 months postpartum receiving herbal medicine will be included. Data will be collected for up to 8 weeks, including demographic information, medical history, herbal medicine prescriptions, AEs, and concomitant medication use. AEs are self-reported by patients, and causality is assessed using the World Health Organization Uppsala Monitoring Centre system and the Naranjo algorithm. Data collection and entry will follow standard operating procedures.

**Results:**

The registry was registered with the Clinical Research Information Service in June 2024 (KCT0009552). Recruitment began in July 2024 across 15 Korean medicine clinics and is planned to continue until June 2027 with a target enrollment of 1000 postpartum patients.

**Conclusions:**

This study represents the first large-scale, multicenter registry examining herbal medicine use during the postpartum period in Korean medicine clinics. By systematically collecting real-world data on AEs associated with postpartum herbal medicine use, we aim to establish a comprehensive safety database for individual herbal medicine and constituent herbs. The findings may support pharmacovigilance of herbal medicine and improve postpartum care outcomes for mothers and infants.

**Trial Registration:**

WHO ICTRP KCT0009552; https://trialsearch.who.int/?TrialID=KCT0009552

**International Registered Report Identifier (IRRID):**

DERR1-10.2196/87543

## Introduction

### Background

Childbirth, although a natural and universal process, imposes considerable stress on the mother’s body, often resulting in a debilitated condition and a low quality of life [1,2]. Studies show that 49% to 94% of women experience at least 1 health issue up to 8 weeks post partum [3,4]. These issues include fatigue [5-9], headache [10-12], musculoskeletal pain [8,13,14], urinary incontinence [15-17], and depression [18-21], often persisting beyond the first year post partum. These prevalent and prolonged health problems significantly affect the well-being of both mothers and their children [22]. This situation highlights the need for safe and effective postpartum care strategies, leading many to consider herbal medicine as a treatment option [23,24].

Herbal medicine offers various potential benefits for postpartum women. Studies have shown that can mitigate postpartum pain [25]. Additionally, when used in conjunction with conventional treatments, herbal medicine may alleviate postpartum depression [26]. In East Asian countries, where herbal medicine is integrated into national health care systems, its use in postpartum care is particularly prevalent, with high satisfaction among consumers. Nevertheless, the lack of safety data on herbal medicine for both mothers and infants remains a considerable concern, possibly deterring some from using herbal medicine [23,27]. For instance, a study in Taiwan found that breastfeeding mothers frequently used HM; however, those consuming traditional Chinese herbs had elevated lead levels in their breast milk, emphasizing the importance of safety monitoring [28]. This global context underscores the urgent need for rigorous safety studies on postpartum herbal medicine use. In Korean medicine practice, postpartum herbal treatment often includes individualized prescriptions derived from traditional formulations such as *Boheo-tang, Ssanghwa-tang, Gunggwijohyeol-eum,* and *Dangguijakyak-san*, which are commonly used to address postpartum symptoms, including fatigue, musculoskeletal pain, and circulatory disturbances. Recent studies have reported that herbal medicine interventions may improve pain, quality of life, and depressive symptoms in postpartum women while demonstrating acceptable safety profiles [25,29,30].

In South Korea, Korean medicine plays an active role in addressing postpartum symptoms, with herbal medicine commonly used alongside acupuncture as the standard treatment method. According to a study on the satisfaction of mothers who received postpartum treatment with Korean medicine during the early postpartum period, 78.68% indicated a willingness to use Korean medicine again in future childbirths [31], while satisfaction with herbal medicine treatment was notably high at 72.13% [32]. Numerous local governments in South Korea support the use of herbal medicine after childbirth by subsidizing expenses, further indicating its perceived value in postpartum care [32].

However, South Korea’s drug use review service does not provide adverse event (AE) information related to herbal medicine. While some national statistics provide estimates on the incidence rate of AEs related to herbal medicine, these figures are based on patient reports or survey data, lacking expert case evaluations and detailed information on specific herbal medicine treatments [33]. Moreover, some reported AEs may not be directly attributable to herbal medicine, underscoring the importance of assessing a clear causal relationship [34]. This lack of comprehensive safety data creates a significant gap in our understanding of the risks associated with postpartum herbal medicine use.

To address these concerns, especially the lack of safety information from official sources, this study aims to establish a registry for those receiving herbal medicine treatment at primary care institutions, specifically Korean medicine clinics. Because Korean medicine clinics account for approximately 96% of Korean medicine institutions in South Korea [35], research based on primary care Korean medicine clinics is crucial for collecting representative clinical data on Korean medicine. Through the systematic collection of data on the constituents of herbal medicine, details of AEs, and causality assessment, we seek to provide evidence for the safety monitoring of herbal medicine administration during the postpartum period.

The primary research questions of this study are as follows: (1) What is the incidence rate of AEs following the use of postpartum herbal medicine? (2) Which herbal medicines and constituent herbs are involved in reported AE cases? (3) What is the causality classification of the observed AEs?

This study represents the first nationwide multicenter registry examining the use of herbal medicine during the postpartum period in Korean medicine clinics across South Korea. By providing comprehensive safety data, this research aims to contribute to evidence-based clinical practice in South Korea and ultimately enhance patient safety for both mothers and infants.

### Study Objective

The objective of the Safety of Herbal Medicine Registry in Korean medicine clinics (SAFEHERE-KM) is to systematically collect and analyze clinical data on AEs related to herbal medicine treatment in postpartum patients in South Korea. This web-based registry will collect patient characteristics, details of herbal medicine prescriptions, and AE information, including a causality assessment of any AEs that arise during herbal medicine treatment using the World Health Organization Uppsala Monitoring Centre causality assessment [36] and the Naranjo algorithm score [37,38]. By establishing AE monitoring databases, this registry further aims to contribute to the development of an active pharmacovigilance system for herbal medicine in South Korea.

## Methods

### Study Design

The SAFEHERE-KM registry is a multicenter, prospective, observational study designed to collect data on routine clinical care and associated AEs in postpartum women receiving herbal medicine treatment at Korean medicine clinics. This study aims to enroll at least 1000 eligible patients between July 2024 and June 2027 based on a previous study suggesting that this sample size rapidly decreases variation when reporting AE incidence [39]. Using empirical observations of postpartum patient visits to participating Korean medicine clinics, we anticipate enrolling approximately 400 participants annually (approximately 27 patients per clinic per year).

The participants are postpartum patients who voluntarily consent to the collection of their clinical data. This study does not introduce specific interventions. Instead, the patients receive individualized herbal medicine treatments as part of their routine postpartum care. Korean medicine doctors prescribe herbal medicine at their discretion without restrictions. This registry focuses on AEs experienced by postpartum women receiving herbal medicine, and infant AEs are not systematically assessed because infants are not enrolled as study participants.

Throughout the treatment period, which may extend up to 8 weeks depending on the duration of prescribed herbal medicine use, we collect data on demographics, medical history, Korean medicine treatment details, herbal medicine prescriptions, AEs, and concomitant medication use. AEs are self-reported by patients via an online survey and recorded in online databases. AEs, including the absence of an AE, will be recorded through scheduled assessments approximately every 2 weeks during the herbal medicine treatment period, with follow-up continuing for up to 8 weeks. The electronic case report form includes predefined fields to record AEs and to indicate whether an event meets the criteria for a serious AE. To ensure consistency in data collection and entry, Korean medicine doctors follow standard operating procedures specifically designed for this registry. All reported AEs, including serious AEs, are reviewed and validated by licensed Korean medicine doctors.

Patients will be recruited from 15 Jayoon Korean medicine clinics, a network specializing in gynecological disorders, located across South Korea. This network provides wide geographical coverage, including 5 clinics each in Seoul and Gyeonggi-do, as well as clinics in Jeju Province, Busan, Incheon, Daejeon, and Daegu (Multimedia Appendix 1).

The registry was registered in the Clinical Research Information Service (KCT0009552). Recruitment started on July 7, 2024.

### Eligibility Criteria

This registry enrolls patients diagnosed with complications predominantly related to the puerperium (O85-O92 of the International Statistical Classification of Diseases-10) or puerperal wind disorder (U32.7 of the Korean Standard Classification of Diseases-8). Puerperal wind disorder indicates a set of symptoms including pain and autonomic disturbance caused by inadequate body care after childbirth [1]. Women who visited the primary Korean medicine clinics within 6 months after giving birth and have been prescribed herbal medicine for postpartum recovery are included. The inclusion and exclusion criteria are presented in Textbox 1.

Inclusion and exclusion criteria.
**Inclusion criteria**
Women aged ≥19 yearsHave visited primary Korean medicine clinics within 6 months post partum (calculated from the date of delivery) and are undergoing herbal medicine treatment for postpartum recovery
**Exclusion criteria**
Did not consent to participateDeemed inappropriate for participation in this study

### Recruitment

Participants will be enrolled in 15 primary Korean medicine clinics that offer postpartum care. Recruitment posters will be placed at the entrance of each clinic to encourage voluntary participation. Health care professionals will explain the study’s purpose and procedures—including data use, confidentiality, and data sharing for analysis—and obtain written informed consent from eligible participants before data collection. Participants may withdraw from the study at any time without any impact on their clinical care. Recruitment began in July 2024 and is currently ongoing across all 15 Korean medicine clinics.

### Study Outcomes

For participants who meet the inclusion criteria and voluntarily sign the written informed consent form, we will assign a study registration number. Subsequently, we will collect data for up to 8 weeks while they consume herbal medicines (Textbox 2).

Table 1 presents the details of the data collection and the study schedule.

Data collected for up to 8 weeks while postpartum patients consume herbal medicines.Demographics: date of birth and ageAnthropometric measurements: height and weightMedical history (maternal health and delivery details): delivery information (date and mode of delivery and gestational age); obstetric history (number of pregnancies, full-term births, preterm births, miscarriages, and surviving children); high-risk pregnancy factors (advanced maternal age [≥35 years], in vitro fertilization, gestational hypertension, and gestational diabetes); and newborn information (demographics, birth details, and feeding methods)Details of herbal medicine prescription: name of prescribed herbal medicine, start date of administration, composition (herbs and doses), total and 1-day dose of herbal medicine, and duration of herbal medicine administrationOther Korean medicine treatments: concurrent treatments, such as acupuncture, moxibustion, cupping, Chuna manipulation, and Korean medicine physical therapyDetails of adverse events (AEs): the occurrence of AEs is monitored at each visit during herbal medicine intake for up to 8 weeks. If an AE occurs, the collected data include the AE start date, symptoms, outcome, severity, actions taken, recurrence after the reintroduction of the suspected herbal medicine, treatment methods for the AE, and concurrent medications. Follow-up telephone interviews may be conducted for detailed information and causality assessments.

**Table 1 table1:** Study schedule.

Time points			Visit 1: baseline^a^		Subsequent visits at 2, 4, 6, and 8 weeks after taking herbal medicine^b,c^		End point: follow-up completion^a,d^
Informed consent			✓				
Demographics			✓				
Diagnosis			✓				
Eligibility screening			✓				
Anthropometrics			✓				
Medical history			✓				
Concomitant medication			✓		✓		✓
**Korean medicine treatment information**							
	Details of the herbal medicine prescription					✓	
	Other Korean medicine treatments					✓	
**Check for adverse events**							
	Occurrence status			✓		✓	
	Details of adverse events^e^			✓		✓	

^a^Data collected from the Korean medicine doctor.

^b^Visits 3, 4, and 5 may be conducted if herbal medicine intake continues, with the process occurring at 2-week intervals for up to 8 weeks.

^c^Data collected from the patient.

^d^Follow-up completion is conducted once data collection of adverse events is finalized or when herbal medicine administration is completed.

^e^Data are collected only in the presence of adverse events. Adverse events represent the primary outcome of this registry.

### Data Management and Quality Control

For data collection, we will use the myTrial Electronic Data Capture system (NIKOM), an electronic case report form system validated by the National Agency for Korean Medicine Innovative Technologies Development. Each clinic’s Korean medicine doctor can access the data entry form via the web server from a remote computer with internet access by logging in using the credentials provided by the website administrator [40]. Each case entered into the registry will be reviewed regularly, and data queries will be generated according to the data monitoring manual. Monitors regularly visit Korean medicine clinics to check the original registry records and research files, and they discuss and resolve any issues with the coinvestigators and principal investigators at each institution. All data collected for this study will be securely stored on a dedicated server with strict access-control permissions.

### Statistical Analysis and Causality Assessment

Statistical analyses will be performed using R (version 4.5.0; R Foundation for Statistical Computing). For participants who withdraw consent for continued follow-up, the data collected until withdrawal will be used in the analysis. For continuous variables, the means and SDs will be presented. Categorical variables will be reported as frequencies and percentages. Herbal medicine exposure will be categorized based on high-frequency prescriptions, major prescription groups, and functional classifications. Patterns of herbal medicine use in AE cases will be explored descriptively. The incidence of AEs will be presented as the proportion of participants experiencing at least 1 AE, and all AEs will be summarized using descriptive statistics. In addition, for cases in which AEs occur, the corresponding prescribed herbal medicine and their constituent herbs will be summarized using frequencies and proportions to describe observed patterns.

For any reported AEs, severity will be determined based on established criteria for assessing AE severity [41]. These criteria are commonly used in clinical safety studies to evaluate the severity of AEs and are applicable to general clinical symptoms regardless of treatment modality. The causality of AEs will be evaluated using both the World Health Organization Uppsala Monitoring Centre causality assessment [36] and the Naranjo algorithm score [37,38], based on the approach used in similar previous studies [42,43]. This evaluation will be carried out by an independent Adverse Reaction Assessment Committee affiliated with the Regional Drug Safety Center at the Korea Institute of Drug Safety and Risk Management.

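### Prescriptions and constituent herbs are summarised only among AE cases, with no AE proportion among exposed women, so the tables cannot support the herb-level safety aim

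*Protocol article*

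**What the plan says.** Four statements in the Protocol article's Statistical Analysis and Causality Assessment section bear on this point.

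- Overall incidence: "The incidence of AEs will be presented as the proportion of participants experiencing at least 1 AE". This is the only AE proportion with a stated cohort denominator.
- Prescriptions and herbs, restricted by the opening of the sentence to cases with an AE: "the corresponding prescribed herbal medicine and their constituent herbs will be summarized using frequencies and proportions to describe observed patterns".
- Patterns of use: "Patterns of herbal medicine use in AE cases will be explored descriptively".
- Exposure grouping: "Herbal medicine exposure will be categorized based on high-frequency prescriptions, major prescription groups, and functional classifications". This sentence is not limited to AE cases, but no AE count is attached to the groups, and constituent herbs are not among them.

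Research question 2 (Introduction, Background) is also framed within cases: "Which herbal medicines and constituent herbs are involved in reported AE cases". The stated aim is wider. The Abstract's Conclusions and the Discussion both say "we aim to establish a comprehensive safety database for individual herbal medicine and constituent herbs", and the Discussion goes on to speak of causal herbs and interaction analysis.

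The exposure data are listed for participants generally in Textbox 2 (Study Outcomes): "name of prescribed herbal medicine, start date of administration, composition (herbs and doses", with total and daily dose and duration. Table 1, footnote e, limits AE details to women with an AE; prescription details carry no such limit. Study Design says that the absence of an AE is also recorded.

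**The concern.** A table of herbs among AE cases holds numerators only. It shows what share of cases had taken a herb, not what share of the women who took the herb had an AE. If a herb has no effect on risk, its share of cases equals its share of prescriptions, so a list ordered by frequency mainly reproduces the prescribing list.

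A safety database for individual medicines and herbs needs the second quantity. Readers of the case-only table may suspect common, harmless herbs and overlook a rarer herb with higher risk. A prospective registry has the advantage over spontaneous reports that it knows who was exposed without harm, and the herb-level analysis as stated does not use that information.

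**Working it through.** The plan gives no AE rate, herb prevalence or risk ratio, so there is no planned figure to reproduce here. N = 1000 is the target in Study Design. All other inputs below are assumptions.

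**Step 1: share of cases with a herb.** Let p be the prevalence of use and RR the risk in users divided by the risk in non-users.

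Share of cases = p × RR / (p × RR + 1 − p)

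- p = 0.90, RR = 1: 0.90 / (0.90 + 0.10) = 90%.
- p = 0.05, RR = 3: 0.15 / (0.15 + 0.95) = 13.6%.

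**Step 2: the same herbs with the exposed denominator.** Assume an overall risk of 8%, so 80 cases in 1000 women.

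- Common herb: 900 users, 0.90 × 80 = 72 cases, 72/900 = 8%.
- Rare herb: risk in non-users = 0.08 / (1 + 0.05 × 2) = 7.3%; risk in users = 3 × 7.27% = 21.8%; 50 × 0.218 = 10.9 cases among 50 users.

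The case-only order is 90% against 13.6%. By risk among the exposed it is 8% against 21.8%, so the order reverses.

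**Step 3: when does the case-only order mislead?** Cases containing a herb = N × prevalence × risk in users. A rarer herb B outranks a commoner herb A only if (risk in B users / risk in A users) > (prevalence of A / prevalence of B). The range at N = 1000:

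| A: use, risk | B: use, risk | Cases A v B | Risk ratio B/A | Ratio needed for B to rank first |
|---|---|---|---|---|
| 80%, 5% | 5%, 5% | 40 v 2.5 | 1 | 16 |
| 80%, 5% | 5%, 20% | 40 v 10 | 4 | 16 |
| 80%, 2% | 5%, 10% | 16 v 5 | 5 | 16 |
| 80%, 10% | 5%, 30% | 80 v 15 | 3 | 16 |
| 60%, 5% | 10%, 20% | 30 v 20 | 4 | 6 |
| 80%, 5% | 30%, 10% | 40 v 30 | 2 | 2.7 |
| 80%, 5% | 30%, 15% | 40 v 45 | 3 | 2.7 |

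In the first row the risks are equal and the 16-fold gap in counts comes from prescribing alone. In the next five the riskier herb ranks second. In the last it ranks first, because its risk ratio exceeds the prevalence ratio.

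**Step 4: precision of the missing figure.** Wilson 95% limits = [x/n + z²/(2n) ± z√(p̂(1 − p̂)/n + z²/(4n²))] / (1 + z²/n), with p̂ = x/n and z = 1.96.

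- 30 users at 8% risk: 30 × 0.08 = 2.4 expected cases; 2/30 gives about 2% to 21%.
- The rare herb of Step 2, rounded to 11/50: about 13% to 35%.

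**The case against.** Five points can be made for the plan.

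1. *Research question 2 is a case-only question, and a case-only table answers it.* This stands. The shortfall is against the wider safety-database aim, not against question 2 as worded.
2. *A reader might infer that the commonest herbs will look worst whatever their risk.* That is too strong. The last row of the table shows a less-used herb ranking first once its risk ratio exceeds the prevalence ratio.
3. *A reader might infer that exposure will be described only in AE cases.* The text does not say so. The exposure-grouping sentence carries no such limit, the case table is introduced as an addition, and treatment patterns are a stated objective in the Abstract. Cohort-wide counts by prescription group may well be reported. However, the text neither links those groups to AE counts nor extends them to constituent herbs.
4. *The tables are called descriptive, and causality is judged case by case with the WHO-UMC and Naranjo methods by an independent committee.* True, and no ranking of herbs is announced. But case assessment supplies no exposed denominator, and a proportion among the exposed is just as descriptive.
5. *Cross-tabulations are usually left to the analysis plan, and herb-level proportions will be imprecise and confounded by co-prescription.* The article does name this analysis and the set it is run in, so the point is about what is stated. The imprecision and confounding are real, and they limit what the added figures can show.

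**Conclusion.** The point holds in a limited form. The stated herb and prescription summaries are numerator-only, and no AE proportion among exposed women is planned for any prescription group or herb. Case-only frequency largely reflects prescribing frequency, so these tables cannot support a safety database for individual medicines and constituent herbs.

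How far they mislead depends on prevalences and risks that the documents do not give. Over the assumed range, the less-used herb needs 2.7 to 16 times the risk of the commoner one before it ranks first. That a case-only share equals prescribing prevalence when a herb has no effect requires no assumed value.

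This should be fixed, but it does not undermine the study. The primary outcome, reported as the overall share of participants with at least one AE, has its proper denominator, and no data are lost.

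**What to change.** Next to the case-only table, for each prescription group and each constituent herb used by a prespecified minimum number of women, report:

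- the number of women exposed;
- the number with at least one AE, for all AEs and for those judged at least possible;
- the proportion with its 95% CI.

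Label these figures exploratory and unadjusted for co-prescribed herbs, and fix the minimum number before the data are analysed.

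The cost is a few more tables from data already collected, with no change to recruitment, data capture or care. The downside is wide intervals in small strata, as the 2/30 example shows; the minimum number of users controls how many such rows appear.
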